### Intervention deliverer training

Intervention deliverers will receive two half days of training from the research team prior to intervention delivery, with a ‘booster’ session during the intervention. The training will include guidance on using the iStep-MS handbook, introduce the COM-B (Capability, Opportunity, Motivation—Behaviour) model of behaviour change,^40^ and cover principles of Cognitive Behavioural Therapy and Motivational Interviewing. Experiential activities will be used to develop and refine intervention delivery, including timing and pacing of sessions. A training handbook will be provided to all intervention deliverers including the training activities and note-taking areas.

### Control group

Control group participants will continue with usual care as normal. Usual care provided may range from no treatment to multidisciplinary holistic care (eg, exercise prescription, massage and oxygen therapy) and, for acute care sites, may also include disease-modifying treatments. Both intervention and control group participants will be asked not to discuss the study with other participants or patients to minimise contamination. To further reduce contamination and encourage engagement with the study, control participants will be provided with the intervention handbook and a Fitbit Charge 6 at the end of the study.

### Study measurements

Data collection will take place remotely to increase accessibility to the study and reduce participant burden. Study measurements will occur at baseline, 3 months post randomisation and 9 months post randomisation. ‘Assessment packs’ will be sent to participants for undertaking these measures consisting of an activPAL4 activity monitor (PAL Technologies, Glasgow, UK) with instructions and an accompanying activity diary, a tape measure with instructions for measuring waist circumference and a pre-paid envelope for returning equipment. Participants will be provided with a £20 shopping gift voucher after completing study measurements at each timepoint.

#### Primary outcome (fatigue)

The primary outcome, fatigue, will be measured using the MFIS, which assesses physical, psychological and cognitive effects of fatigue.^41
42^ The MFIS has high internal consistency, excellent test–retest reliability and good construct validity in PwMS.^27
42^ The MFIS items will be aggregated into physical, cognitive and psychosocial subscale scores (with ranges of 0–36, 0–40 and 0–8, respectively), and a total MFIS score (range of 0–84). Higher scores indicate greater impact of fatigue.

#### Secondary outcomes

##### Sitting, standing and stepping

An activPAL4 activity monitor will be worn on the anterior aspect of the thigh at each timepoint to measure daily sitting, standing and stepping time, prolonged sitting, number of steps and number of sit-to-upright transitions over seven full consecutive days. The activPAL provides valid data for these outcomes in PwMS.^43
44^ Sleep and wake times will be recorded by participants in a diary, in addition to times that the activPAL is removed. ActivPAL data will be downloaded using proprietary software (PAL Technologies, Glasgow, Scotland) and processed with Processing PAL V1.41—21022022 (University of Leicester, UK) to identify valid waking wear data.^45^ Criteria to confirm a valid wear day will be ≥10 hours of waking wear time, <95% of time spent in a single event (ie, sitting, standing or stepping) and ≥250 steps.

##### Waist circumference

An adjustable tape measure will be used by participants to measure their waist circumference three times to the nearest 0.1 cm at the level of their umbilicus following gentle expiration. The mean of these three measures will be used for analysis.

##### Quality of life

The EuroQol 5 Dimension 5 Level (EQ-5D-5L) will be used to assess QoL across five dimensions: mobility, self-care, usual activities, pain/discomfort and anxiety/depression.^46
47^ The EQ-5D-5L provides good discriminatory capacity in MS.^46^ Responses will be answered using a 5-point Likert scale, which will be used to derive index values for each dimension and an overall England-specific value set. Overall health will be rated on a 0–100 visual analogue scale.^47^ Higher scores reflect greater QoL across all items.

##### Impact of MS

The physical and psychological impact of MS during the past 2 weeks will be assessed using the 29-item Multiple Sclerosis Impact Scale (MSIS-29).^48^ The MSIS-29 has good to excellent reliability and demonstrated construct validity with other measures of physical and psychological health in PwMS.^48^ Physical and psychological impact scores are calculated by summing their respective items and then transforming to a score on a scale of 0–100. Higher scores on the MSIS indicate greater impact of MS on day-to-day life.

##### Walking capability

The Twelve Item MS Walking Scale (MSWS-12) will be used to measure balance, use of support, speed, distance and automaticity aspects of walking capability over the past 2 weeks. This questionnaire has excellent validity and test–retest reliability, and high internal consistency across a range of disability severities in PwMS.^49^ The item responses are summed, giving a total out of 60 and then transformed on a scale of 0–100. A higher MSWS-12 score reflects poorer walking capability.

##### Pain

Pain will be assessed using the pain section of the EQ-5D-5L on a 5-point Likert scale, with higher scores indicating more pain.

##### Self-efficacy

The Multiple Sclerosis Self-Efficacy Scale (MSSE) measures confidence in behaviours for Activities of Daily Living and managing disease symptoms, reactions to MS-related limitations, and impact of MS on life activities.^50^ The MSSE has good construct validity and test–retest reliability.^50^ Item scores are summed to create a self-efficacy score for Function, Symptom and Control subscales. A total score is also created with higher scores indicating greater self-efficacy.

### Statistical analysis

Baseline characteristics for each group and the whole sample will be described descriptively. The primary analysis will be ‘intention-to-treat’, analysing participants with available outcome data in their randomised groups regardless of adherence to the trial. The primary analysis will identify if the intervention and control lead to a difference in MFIS score at 9 months post randomisation. Differences in MFIS scores between groups will be estimated using a linear regression model, adjusting for stratification factors, baseline MFIS score and other relevant prognostic factors. Potential clustering with randomising sites will be accounted for using robust SEs. Adjusted mean differences between groups will be presented with 95% CI and p values. The pattern of missingness will be examined and, if appropriate, a sensitivity analysis will be undertaken using a multiple imputation model for missing data.

Secondary outcomes at 3 and 9 months will be analysed using regression models appropriate to the outcome distribution (eg, linear for continuous data, logistic for binary data), controlling for the baseline level of the outcome (where collected), stratification factors and key prognostic factors, as per the primary outcome. The effect of non-adherence (<70% completion of consultations) with the allocated intervention will be evaluated using per-protocol analyses.

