**Methods and analysis:**

This is a multicentre, two-arm randomised controlled superiority trial with embedded economic and process evaluations. The study will take place across South-East England in acute and community National Health Service settings and charity-funded MS and neurological therapy centres. Intervention deliverers will include a range of healthcare staff such as physiotherapists, occupational therapists, therapy assistants, nurses and exercise therapists. A target sample size of n=198 participants will be randomised 1:1 to the intervention (iStep-MS behaviour change intervention plus usual care) or control (usual care only) arms. Participants will be adults with any type of MS, experiencing MS-related fatigue, relapse-free for >3 months, with a Self-Reported Disability Status Scale category of ≤3.5 (no disability to moderate disability) or 4–6.5 (significant disability). The iStep-MS intervention includes four one-to-one consultation sessions in-person or online with an intervention deliverer over 3 months, incorporating behaviour change techniques aimed at increasing physical activity and reducing sedentary behaviour. The consultations are supported by a handbook designed to help individuals with MS set goals and achieve behavioural changes and a wearable activity tracker for self-monitoring. Outcomes (assessed at baseline, 3 months and 9 months) include self-reported fatigue, quality of life, MS-impact, walking capability, pain, self-efficacy and waist circumference. Sitting, standing and stepping will be measured over 8 days using the activPAL4 device. A process evaluation will assess intervention acceptability, adherence and fidelity, including questionnaires and focus groups with participants and deliverers. A cost-effectiveness analysis will evaluate the value for money of the intervention against usual care.

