### Sample size

Sample size was calculated based on the primary outcome, fatigue. A minimum clinically important difference of 8.11 on the MFIS^32^ and a SD of 18.1 from the iStep-MS feasibility study^27^ results in an effect size of d=0.45. To detect this effect with 80% power and α=0.05, n=158 would be required. To account for 20% dropout, a target of 198 participants (n=99 in each arm) will be recruited.

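### The primary analysis is a complete-case regression at 9 months that leaves out the 3-month MFIS, so it can be biased if dropout depends on 3-month response differently by arm

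*Protocol article*

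**What the plan says.** All references are to the protocol article.

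- **Analysis set (Statistical analysis):** the intention-to-treat analysis means "analysing participants with available outcome data in their randomised groups regardless of adherence to the trial". Anyone without a 9-month MFIS is therefore left out.
- **Time point (Statistical analysis):** "The primary analysis will identify if the intervention and control lead to a difference in MFIS score at 9 months post randomisation".
- **Model (Statistical analysis):** the difference is "estimated using a linear regression model, adjusting for stratification factors, baseline MFIS score and other relevant prognostic factors". Robust standard errors are planned for site. The 3-month MFIS is not mentioned.
- **Missing data (Statistical analysis):** the pattern of missingness is examined and, "if appropriate, a sensitivity analysis will be undertaken using a multiple imputation model for missing data".
- **Data collected:** "Outcomes (assessed at baseline, 3 months and 9 months) include self-reported fatigue" (Abstract), and "Study measurements will occur at baseline, 3 months post randomisation and 9 months post randomisation" (Study measurements).
- **Expected loss (Sample size):** "To account for 20% dropout, a target of 198 participants".

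**The concern.** A regression on 9-month completers is valid only if, given arm, baseline MFIS and the other covariates, having a 9-month score is unrelated to what that score would have been. A link between dropout and fatigue at 3 months breaks this condition, because 3-month and 9-month fatigue are correlated beyond what baseline explains.

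The design makes such a link plausible, and also makes it plausible that it differs by arm:

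- The trial is unblinded and the outcome is self-reported.
- The last consultation falls at about week 11, so the 3-month score records perceived response just before a six-month interval without contact sessions.
- Reasons to stay differ by arm. Control participants receive the handbook and tracker at the end of the study, whereas intervention participants already have them.

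At stake is the headline estimate. If the conditional imputation analysis disagrees with the primary result, the complete-case figure still stands as primary. Whether imputation is appropriate would also be decided after missingness has been seen.

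**Working it through.** **1. The plan's own figures.** Inputs from Sample size: difference 8.11, SD 18.1, 80% power, α = 0.05 (two-sided reproduces the result), 20% dropout.

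- n per arm = 2 × (1.960 + 0.842)² × 18.1² / 8.11² = 78.2, rounded up to 79, so 158 in total.
- 158 / 0.8 = 197.5, rounded up to 198.

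Both figures reproduce. About 40 of 198 participants (198 − 158) are expected to have no 9-month score.

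**2. Assumptions not in the documents.** Baseline–3-month, baseline–9-month and 3–9-month correlations (r01, r02, r12) of 0.5/0.5/0.6, 0.6/0.6/0.7 and 0.7/0.7/0.8. A log-odds slope of dropout on 3-month MFIS (b) of 0.5 or 1.0 per SD. About 20% missing at 9 months, with 3-month MFIS seen for everyone (the best case for the remedy). No site clustering. The true effects are −8.11 at 9 months and −6.19 at 3 months (the feasibility result quoted in Background).

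**3. Hand approximation, one arm affected.** To first order, with dropout proportion p, the completers' mean in that arm shifts by about −b × p × (r12 − r01 × r02) × SD.

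- b = 1.0, correlations 0.6/0.6/0.7: −1.0 × 0.2 × (0.7 − 0.36) × 18.1 = −1.23.
- b = 0.5, same correlations: −0.62.

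The same shift in both arms roughly cancels. Opposite shifts add. Halving the response-related part of p halves the bias.

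**4. Simulation (4000 trials per scenario, 99 per arm).** A negative bias overstates benefit.

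| Dropout depends on | Bias, complete-case | Bias, using 3-month MFIS |
|---|---|---|
| nothing, or baseline MFIS | about 0 | about 0 |
| 3-month MFIS, equally in both arms | 0.0 to +0.2 | about 0 |
| 3-month MFIS, intervention arm only | −0.5 to −1.2 | about 0 |
| 3-month MFIS, opposite directions by arm | −1.0 to −2.2 | about 0 |
| unseen 9-month MFIS, intervention arm only | −0.8 to −2.3 | −0.5 to −1.8 |

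Residuals in the first four rows are at most 0.08. With an empirical SE of 2.0 to 2.5, simulation error is about 2.5 / √4000 = 0.04.

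- One arm: 0.5 / 8.11 = 6% and 1.2 / 8.11 = 15% of the target, or about a quarter to a half of the SE (0.51 / 2.07 = 0.25; 1.17 / 2.30 = 0.51).
- Opposite directions: up to 2.2 / 8.11 = 27%.
- The sign reverses if good responders leave the intervention arm.

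**5. Early leavers.** In a separate run with correlations 0.60/0.55/0.75, the one-arm bias was −1.18 when all dropouts left after month 3. It was −0.65 when half left earlier at random, and −0.34 when three quarters did.

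**6. Precision under random dropout.** Variance factor = 1 − 0.2 × (partial r)², where the partial r is between 3- and 9-month MFIS given baseline.

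- 0.5/0.5/0.6: partial r = 0.35 / 0.75 = 0.467; factor 0.956; SE 2% lower.
- 0.7/0.7/0.8: partial r = 0.31 / 0.51 = 0.608; factor 0.926; SE 4% lower.

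This equals about 7 to 13 extra completers on 158 (158 / 0.956 − 158 = 7; 158 / 0.926 − 158 = 13). If half the dropouts leave before month 3, the gain is about 1% (SE 2.43 against 2.40).

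**The case against.** The strongest reply is that regression on available data, backed by an imputation sensitivity analysis, is a recognised approach, and that nothing in the article shows dropout will differ by arm. The sizes rest on assumed correlations and slopes, and the opposite-direction case is extreme. Retention is also addressed: data collection is remote, each assessment earns a £20 voucher, and controls are offered the handbook and tracker at the end. The imputation model could include 3-month MFIS, and its contents properly belong to an analysis plan that is not shown.

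Much of this stands. A reader might infer that dropout will bias the result, or that benefit will be exaggerated. The documents support neither: bias needs a response link that differs by arm, and its sign depends on who leaves. A reader might also infer that the 3-month data are thrown away. That goes too far, since 3-month assessments also serve the secondary regressions and the economic evaluation, and the lost precision is a few per cent at most. The lack of a stated not-at-random analysis is not a fault in a condensed article.

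The reply does not remove the point that the article positively fixes which analysis is primary. A conditional sensitivity analysis cannot replace a primary estimate that rests on the stronger assumption. The repeated-measures alternative is only a partial cure, because it does not correct dropout driven by unobserved 9-month scores.

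**Conclusion.** The point holds as a conditional risk. The stated primary analysis omits an observed score that would guard against one plausible form of dropout.

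With 20% dropout, all of it after month 3, the bias is roughly 0.5 to 1.2 MFIS points (6% to 15% of 8.11) if dropout follows 3-month response in one arm, and up to about 2 points in the extreme opposite-direction case. It is at most about 0.2 if the link is equal in both arms and about 0 if dropout is random or related to baseline. It roughly halves if half the dropouts leave before month 3. The direction cannot be known in advance.

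These sizes rest on the assumed correlations (0.5 to 0.8) and slopes (0.5 to 1.0 per SD). The case for change is protection against bias. The SE gain of about 1% to 4% would not justify it alone. The sample size calculation is unaffected.

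**What to change.** Make one of these the primary estimate, fixed before outcome data are examined:

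- the 9-month contrast from a likelihood-based repeated-measures model of 3- and 9-month MFIS, with arm-by-time, baseline MFIS-by-time, the stratification factors and an unstructured covariance; or
- the planned 9-month regression after multiple imputation, done unconditionally and by arm, with 3-month MFIS in the imputation model. This route keeps the planned regression and its robust standard errors as they are.

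Keep the complete-case regression as a sensitivity analysis.

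The cost is a change of wording in the protocol and analysis plan and a slightly more complex model. No extra data or participants are needed. The write-up should state that neither option corrects dropout driven by unobserved 9-month scores.

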### Health economic evaluation

The economic evaluation will involve cost-effectiveness analysis (from baseline to 9 months) to examine value for money of iStep-MS against usual care. The perspective for the analysis will be NHS and personal social services, and patient.^51^ The resource use will comprise: (a) training for deliverers; (b) consultations provided by deliverers; (c) handbooks and wearable trackers and (d) health and personal social service use via a modified Client Service Receipt Inventory (CSRI),^52^ which will be completed by participants at baseline, 3 and 9 months. Completion of the CSRI has been validated against General Practitioner case records.^53^ Out of pocket expenses related to physical activity sessions (eg, transport costs) will be collected via self-report at baseline, 3 and 9 months. Resource use data will be collected through interviews with trial and intervention staff (including collecting information on staff time and money spent on each activity) and review of trial management records. Unit costs will be taken from the NHS reference costs,^54^ standard unit costs^55^ and published literature.

The key outcome will be an incremental cost per Quality-Adjusted Life-Year (QALY), which will be based on the EQ-5D-5L. There will also be exploratory analysis of QALY estimation based on MS-specific health states using the eight-dimension Multiple Sclerosis Impact Scale (MSIS-8D), which is derived from the MSIS-29.^56^ Cost per change in fatigue will also be measured. Analyses will show mean total costs and mean utilities by trial arm and differences between trial arms. Uncertainty will be represented in cost-effectiveness acceptability curves for intervention vs control. Subgroup analysis will be undertaken using the trial stratification factors. If other factors are found to be significant in the subgroup statistical analyses, then it will be considered if it is possible to use these and whether there is a good economic/ policy reason to do so.

### Process evaluation

A mixed-methods process evaluation will be undertaken to explore intervention fidelity, adherence and acceptability. Fidelity of intervention implementation will be evaluated following the fidelity in complex rehabilitation interventions guidelines.^57
58^ Participant attendance at iStep-MS consultation sessions will be recorded by intervention deliverers. At least 10% of each intervention deliverer’s consultations will be audio-recorded and rated by a researcher against a checklist for content delivery (online supplemental material 2). Delivery of ≥70% of expected content will be considered acceptable.^58^ Fidelity to delivery skills will be assessed and considered acceptable if competence is scored at level 2 (‘Evidence of competence, but lack of consistency’) to 6 (‘Excellent performance, effective management of difficulties’) in each skill category. The percentage of handbook sections completed by participants will be assessed against a checklist (online supplemental material 3) using photographs from all handbook sections for ≥20% of intervention participants.

A subsample of intervention participants (n=24) and deliverers (n=12) from across the study sites will take part in focus groups following 3 month measurement and intervention delivery periods to explore acceptability and experiences of taking part in iStep-MS. Focus group topics will be guided by the previous iStep-MS fidelity evaluation^58^ and the Theoretical Framework of Acceptability;^59
60^ see online supplemental material 4. The qualitative data will be analysed using the Framework Method of Analysis.^59^

### Data management

All study documentation containing identifiable participant data will be managed in accordance with ICH–GCP (International Council for Harmonisation–Good Clinical Practice), the UK Policy Framework for Health and Social Care Research, the Data Protection Act 2018 and most recent UK General Data Protection Regulation. Each participant will be allocated a unique study ID that will be used in data records to preserve anonymity. Study paperwork will be stored in locked filing cabinets at the study sites and will only be accessible to authorised study personnel. Study data will be captured electronically in a secure password-protected bespoke REDcap database system. Pseudonymised data for the health economic evaluation will be securely transferred to the health economics researchers for analysis, which will be held in password protected files.

Audio recordings from focus groups and consultation sessions will be made using the recording feature of Microsoft Teams, on a smartphone or tablet or with an encrypted Dictaphone. The recordings will be transcribed using the automatic transcription function of Microsoft Teams or proprietary Dictaphone software and manually checked by a researcher. Transcripts will be anonymised or assigned a pseudonym and saved onto a secure university network server. The audio recordings will then be deleted.

### Trial monitoring

A Trial Steering Committee (TSC) will ensure that appropriate ethical approvals are obtained and will monitor progress of the trial, protocol adherence, substantial protocol amendments and patient safety. The TSC will also receive and review the progress and accruing data of the trial. The Committee will comprise an independent chair, an independent expert in the study area, an independent statistician, a public member with MS and study investigators.

### Adverse event reporting and harms

Any adverse events (AEs) reported by participants, such as falls, illness or skin irritation from the activPAL or Fitbit, will be recorded within the trial database during the study. At the 3 month and 9 month post randomisation timepoints, participants will complete a questionnaire asking if they have experienced a fall, relapse or AE since their last point of contact in the study. If a participant reports an AE directly to their study site, a delegated staff member will report it to the Principal Investigator and central research team for it to be recorded within the trial database. Data recorded on AEs will include date of onset, resolution, outcome, severity and causality. Expectedness and cause (probable, possible, unlikely or unrelated to the trial) of the AE will be assessed by the Principal Investigator or the central research team.

Serious adverse events (SAEs) (AEs which are life-threatening, resulting in hospitalisation, death or prolonged and worsened impairment) should be reported to the Chief Investigator by the site Principal Investigator or researcher within 24 hours of becoming aware of the event. The Chief Investigator will be responsible for notifying the trial Sponsor of an SAE within 48 hours and the NHS Research Ethics Committee that gave a favourable opinion of the research within 15 days of becoming aware of the event. A ‘directly attributable’ SAE will only be recorded and reported if the event occurs during contact time with an intervention deliverer or while undertaking physical activity as part of the intervention. Participants who experience an SAE that affects their continued safety or significantly affects the conduct or outcomes of the study will be withdrawn.

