### iStep-MS consultations

There will be four one-to-one physical activity and sedentary behaviour consultation sessions delivered to each participant approximately 1, 3, 7 and 11 weeks after randomisation. The sessions are expected to last approximately 45–60 min. Indicative content of the sessions is shown in box 1. Intervention deliverers will be healthcare staff with varying qualification levels who provide MS care at the study sites. Job roles may include physiotherapists, occupational therapists, therapy assistants, nurses and exercise professionals. All deliverers will receive behaviour change training from the research team specific to the iStep-MS intervention. It is intended that participants will be supported by the same deliverer throughout all consultations where possible, to create a supportive environment, build rapport and improve confidence.^27^ Consultations will take place in-person or via online video call depending on the options each site is able to offer and participant preference.

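### AE ascertainment is unequal between arms: questionnaire and site-reported events share one database with no source listed, and only iStep-MS participants have scheduled sessions with site staff

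*Protocol article*

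**What the plan says.** The protocol article, under Adverse event reporting and harms, describes two routes.

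- **Questionnaire, both arms.** "At the 3 month and 9 month post randomisation timepoints, participants will complete a questionnaire asking if they have experienced a fall, relapse or AE". The period covered is the time "since their last point of contact in the study".
- **Report to the site, at any time.** "If a participant reports an AE directly to their study site, a delegated staff member will report it to the Principal Investigator", and to the central team, so that it can be entered in the database.

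AEs from participants "will be recorded within the trial database during the study". The items named for each AE are when it began and resolved, its outcome, its severity and its causality. The route by which it was reported is not named.

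Contact with site staff differs by arm. Under iStep-MS consultations, the four one-to-one sessions are "delivered to each participant approximately 1, 3, 7 and 11 weeks after randomisation", which in that section means each intervention participant. They last about 45 to 60 minutes, and "Intervention deliverers will be healthcare staff with varying qualification levels who provide MS care at the study sites". Under Control group, "Control group participants will continue with usual care as normal", and usual care may be anything from no treatment to multidisciplinary care. Under Study measurements, data are collected remotely, so neither arm has a scheduled site visit for outcomes. The trial is unblinded (Study design).

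**The concern.** A comparison of AEs between arms is interpretable only if an event has the same chance of being recorded in each arm. Here the intervention arm has four scheduled conversations with people who work at the sites, and the control arm has no scheduled counterpart. According to Box 1, the sessions cover barriers, setbacks and coping with relapse or worsening illness, so a fall or relapse may well be mentioned.

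The questionnaire wording adds a second imbalance. If a consultation is a study contact, an intervention participant's 3-month questionnaire may cover only the time since the week-11 session, while a control participant's covers the whole period.

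At stake is how any difference in falls, relapses or other AEs would be read, both in the final report and by the Trial Steering Committee, which monitors safety and reviews accruing data. An apparent excess could be a reporting effect, and a true excess could be hidden.

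**Working it through.** The article states no AE rate and no AE-based figure, so there is none to reproduce. The only plan figure used below is 99 per arm (Sample size: 158/0.80 = 197.5, rounded up to 198). The rest illustrates how far and in which direction the recording rule can move a ratio whose true value is 1.

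**Inputs from the article:** sessions at about weeks 1, 3, 7 and 11; questionnaires at 3 and 9 months, taken as weeks 13 and 39.

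**Assumptions, not in the article:**
- *s*, the chance that the questionnaire captures an event within its window: 0.60 to 0.95, equal in both arms.
- *v*, the chance that an intervention participant's event is volunteered at a session: 0 to 0.5.
- No control event is volunteered, which is the choice most favourable to an upward bias.
- Events are spread evenly over time, and true risk is equal in the two arms.

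**A. The questionnaire looks back in full in both arms.** Control capture is s. Intervention capture is 1 − (1 − s)(1 − v).
- 3-month ratio = [1 − (1 − s)(1 − v)]/s. With s = 0.60 and v = 0.5: 0.80/0.60 = 1.33. With s = 0.95 and v = 0.5: 0.975/0.95 = 1.03.
- This lets every event up to week 13 be volunteered. Counting only events before week 11, the largest value becomes [(11/13)(0.80) + (2/13)(0.60)]/0.60 = 0.769/0.60 = 1.28.
- 9-month ratio = {(11/39)[1 − (1 − s)(1 − v)] + (28/39)s}/s. With s = 0.60 and v = 0.5: 0.656/0.60 = 1.09.

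**B. A consultation counts as the last contact.** The intervention arm's 3-month questionnaire then covers about 2 of 13 weeks, and earlier events are recorded only if volunteered.
- 3-month ratio = [(11/13)v + (2/13)s]/s. With v = 0: 2/13 = 0.15. With s = 0.60 and v = 0.5: 0.515/0.60 = 0.86.
- 9-month ratio = [(11/39)v + (28/39)s]/s. With v = 0: 28/39 = 0.72. With s = 0.60 and v = 0.5: 0.572/0.60 = 0.95.
- Both ratios equal 1 when v = s and exceed 1 only when v > s.

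Recorded intervention-to-control ratio with no true difference, over s = 0.60 to 0.95:

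| Reading | v = 0 | v = 0.3 | v = 0.5 |
|---|---|---|---|
| A, 3 months | 1.00 | 1.02–1.20 | 1.03–1.33 |
| A, 9 months | 1.00 | 1.00–1.06 | 1.01–1.09 |
| B, 3 months | 0.15 | 0.42–0.58 | 0.60–0.86 |
| B, 9 months | 0.72 | 0.81–0.86 | 0.87–0.95 |

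**Chance of a nominally significant false signal under A.** With 99 per arm and an assumed true 3-month risk of 20% to 40%, the chance of p < 0.05 is at most about 24% (s = 0.60, v = 0.5, risk 40%: 32% recorded against 24%). In most settings it is below 10%.

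**Questionnaire events only.** With one fixed window in both arms, each arm has capture s and the ratio is 1.00. Under reading B, with the current wording kept, the 3-month questionnaire-only ratio is 0.15. Restricting to the questionnaire without fixing its window would therefore make matters worse.

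**The case against.** A reader might infer that iStep-MS will appear to cause more AEs even if it causes none. The document does not support that. A volunteered event adds to the count only if the questionnaire would have missed it. Control participants can also report to their site, and some have substantial usual care. Box 1 frames barriers and setbacks around behaviour goals, and deliverers are not said to ask about AEs. The look-back wording could reverse the sign. Nor does it follow that the trial could say nothing about relative safety: both arms complete the questionnaire twice, and onset, severity and causality are recorded.

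The other main objection is that the article plans no between-arm AE comparison. Recording events from every route is ordinary safety practice, and tabulation by source belongs in the analysis plan, which is not shown. This is right about the analysis: no pooled comparison is stated, so none can be criticised. The list of AE items may also be condensed from a fuller form.

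What stands is the point about collection. The article itself sets the two routes, the look-back wording and the unequal contact. An analysis plan can choose which events to compare, but it cannot reliably recover a source that was not captured or a window that differed between arms.

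**Conclusion.** The concern holds as a weakness in how AEs are ascertained, not as a prediction that one arm will look worse. Opportunity to report is unequal by design in an unblinded trial, and any comparison drawn from the combined records could be biased in either direction.

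The size cannot be known from the document. Under the assumed capture rates an upward bias is modest and is diluted by 9 months. The downward bias at 3 months could be much larger, but only if a consultation is treated as the last point of contact, which the article neither says nor excludes. The change is worth making because it is cheap and is best made before the data are collected.

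**What to change.** 1. Add a source field to each AE record: questionnaire, site-reported, or both.
2. Word the questionnaire with the same fixed window in both arms: since randomisation at 3 months, and since the 3-month assessment at 9 months. Ask participants to include events they have already reported to site staff.
3. State that the between-arm comparison of falls, relapses and AEs uses questionnaire-reported events, and that an event reported by both routes counts once.
4. List site-reported-only events and all SAEs by arm for safety review.

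Steps 2 and 3 belong together, because step 3 without step 2 could worsen the bias.

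The cost is one database field, a change to the questionnaire wording and a few sentences in the harms section. The downside is that non-serious events reported only to sites leave the comparative table, although they stay in the listings. Equal questionnaire capture in the two arms remains an assumption in an unblinded trial. The change removes the imbalance that the recording rule creates, but not every possible difference in reporting.
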